### Ethical approval

This trial has been approved by Medical Ethics Committee of the Second Affiliated Hospital of Nanjing Medical University and all ethics committee at other participating centers.

## Discussion

Injection sclerotherapy dates back at least one century and has been regarded as a simple and convenient office procedure for internal hemorrhoids.^25^ However, the development of this minimally invasive therapy has been used much less than before because of ectopic injection. The CAES was coined as an innovation technique for having advantages in accurately controlling the injection angle, direction, and depth under direct vision of flexible endoscope. The core value of CAES for internal hemorrhoids and rectal prolapse is to provide precise therapy, reduce the iatrogenic injuries, and avoid pain during and after therapy. Our pilot studies demonstrated that CAES based on long injection needle is an effective, safe, and convenient operation technique^12,16^; 100% of participants who underwent CAES showed sustained clinical efficacy within the 3-month follow-up, with no severe or obvious complications related to CAES.^16^ The CAES is helpful to avoid doctor’s face close to patient’s anus. Notedly, gastroscope is recommended only for CAES with short injection needle where retroflection of the endoscope is necessary, of which the softer material and thinner diameter make it more flexible in operation. We have to clarify that there is no necessary to perform retroflection when using colonoscope and long needle in pracitce.

The length of injection needle is controversial in the process of injection sclerotherapy. Tomiki and colleagues^15^ suggested that short needle can avoid inserting into dangerous areas such as mucosal muscular layer. They recommend using 3-mm short needle to reduce ectopic injection.^15^ On the contrary, the short injection needle was not suggested in CAES because its short length needs to multiple-site injections, which may lead to more mucosal injury, potential inflammation, and complications such as artificial ulcer and secondary bleeding due to the shallow injection depth and imprecise operation caused by the retroflection of endoscope. Reasonably, the long injection needle would bring more benefit to patients and endoscopists, which requires data to prove its authenticity.

Studies on the treatment of hemorrhoid disease have shown considerable heterogeneity because of the variety of outcome measurements. The outcome measurements we chose based on the Core Outcome Set for hemorrhoid disease developed by Breukink and colleagues and the European Society of Coloproctology may improve the quality of our research and enhance the analysis of evidence.^7^ A previous research indicated that the physical appearance of the postoperative anal cushions and patients’ symptoms are poorly correlated, meaning anorectal visualization is not a reliable surrogate of success.^26^ Our clinical experience and principal management for hemorrhoids shows that there is no need to review colonoscopy within half a year after CAES treatment. We therefore used a simple, dichotomized definition of recurrence based on Shanmugam and colleagues’^18^ systematic review definition and measured this at 24 weeks post-CAES.

Patients might benefit much more from CAES than traditional office injection sclerotherapy. The diagnosis of hemorrhoids is not difficult, but misdiagnosis and missed diagnosis often exist in clinical practice. It is not rare to misdiagnose malignant tumors as hemorrhoids.^1,5,27^ Patients with ulcerative colitis and Crohn’s disease were reported to have hemorrhoids, suggesting that colonoscopy examination before CAES will be conducive to early diagnosis of inflammatory bowel disease with hemorrhoid symptoms by determining intestinal lesions.^28^ In addition, hematochezia can result from hemorrhoids, diverticulosis, mucosal abnormality/colitis, polyp or multiple polyps, tumor, solitary ulcers, and other diseases.^12,29^ Therefore, CAES was originally designed not only for patients who had been clearly diagnosed hemorrhoids that needed therapy but for patients who needed colonoscopy to clarify a diagnosis and then performed possible CAES (patients diagnosed of internal hemorrhoids under this colonoscopy) during the same opportunity of colonoscopy. Moreover, 30.0% and 41.6% of patients underwent other endoscopic procedures such as polypectomy, neoplasia resection, excision of anal papilla fibroma, biopsy during CAES in our previous studies,^12,16^ which undoubtedly reduced patients’ medical costs and the physical and mental pain caused by anesthesia, intestinal preparation

There are some limitations in this study, which were not designed to compare the efficacy and safety of other office-based procedures like RBL. Furthermore, this is a single-blind design study, because the visualization of the operation cannot be double-blind.

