### Randomization

A remote, web-based randomization system (Medical Data, Unimed Scientific, Inc, Wuxi, China) will be used to generate random numbers for the participants. Patients will be divided into the long injection needle group (n = 578) and the short injection needle group (n = 578) at a ratio of 1:1 according to the random numbers. The Medical Data application program (APP; System developed by Unimed Scientific, Inc, Wuxi, China) will directly display the randomly assigned treatment group to instruct physicians to select injection needles for CAES.

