The sclerosing agent in the present study is Lauromacrogol injection (Tianyu Pharmaceutical, Xi’an, China). Researchers are required to upload the endoscopy report in details after CAES, including the description on procedure, type of needle, and endoscopic images as shown in Supplementary Table 1 to the Medical Data APP. Since 2014 up to 2019, the CAES has been used in more than 500 hospitals for hemorrhoids in China. Researchers involved in the present trial are required to be advanced endoscopists. All researchers must be trained by watching the standard CAES video from [name] and endoscopy training from advanced CAES experts. At least 5 cases of CAES were performed prior to recruiting case to this study for each researcher.

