### Outcome measures

The outcome measures and the follow-up points are shown in detail in the Supplementary Tables. The primary outcome measure is “the recurrence rate,” defined as the proportion of patients with recurrent hemorrhoids at 24 weeks post-CAES, as derived from patients’ self-reported answer to the following questions simplified by the Shanmugam and colleagues’^18^ criteria: “At the moment, do you feel your symptom (anal pain, prolapse, itching, soiling and blood loss) from your hemorrhoids are (1) cured or improved compared with before starting treatment or (2) unchanged or worse compared with before starting treatment.” Patients will be considered to have recurrent hemorrhoids when any of the following are recorded^19^: (1) “Unchanged or worse compared with before starting treatment” at 24th week as reported by the patient, or (2) seeking repeat CAES treatment, alternative non-surgical/surgical treatments for internal hemorrhoids within 24 weeks (except medication treatment), or (3) presence of any symptoms or events that strongly indicated recurrent hemorrhoids among patients not meeting (1) or (2). During follow-up, endoscopic examination will be performed when the patients develop uncontrollable anal pain, bleeding, or when repeat CAES is necessary because of recurrence.

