### Safety assessment and management

The AEs are classified as mild, moderate, and severe according to the degree of impact on daily activity. The relationship between AEs and CAES is divided into five grades, including absolutely relevant, possibly relevant, possibly irrelevant, absolutely irrelevant, and immeasurably, according to the basis of the occurrence time of AEs, symptoms and changes in AEs after cassation/repetition of CAES.

Previous study has shown that CAES using long needle is a safe technique with very few AEs.^12,16^ However, possible risks should be considered for physicians who do not control the angle, direction, and depth of injection under endoscopic view as well. In general, mild AEs caused by CAES can be alleviated by themselves without special intervention. In addition to the following situations: (1) unexplained large amount of bleeding or severe pain after CAES, with ineffective conservative treatments, endoscopic examination should be taken to find etiology and do corresponding treatments; (2) rational use of antibiotics when suspected postoperative infection aggravates; (3) continuous difficulty in passing gas after CAES, enema, blinden, subcutaneous, or intramuscular injection of neostigmine will be helpful; and (4) repeat CAES or other treatment options should be adopted if symptoms are not improved significantly or even worse than before, or the recurrence of internal hemorrhoids.

In case of SAEs, treatments should be given according to the patient’s condition. Timely report to the project sponsor, ethics committee, blinding unit, regulatory authority in accordance with the Sponsor’s Standard Operating Procedures (SOPs). Site staff will be responsible for reporting SAEs and complete an SAE form. The possible most important SAEs is deep infection with pain, swollen, and redness after CAES. Antibiotics should be used in time to control the infection.

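### The visible operation justifies an unblinded operator, not unblinded recording of week-24 recurrence; criterion (3) of the primary outcome is an open judgement with no stated masking.

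*Protocol article*

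**What the plan says.** **Blinding.** The Protocol article calls the trial single-blind in the Abstract, Background and Methods. The only reason given is in the Discussion: "this is a single-blind design study, because the visualization of the operation cannot be double-blind". The article does not name the blinded party; the patient is the natural reading.

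**Who knows the needle.** Under Randomization, the app "will directly display the randomly assigned treatment group to instruct physicians to select injection needles for CAES". Under Concept and methods of CAES: "Researchers are required to upload the endoscopy report in details after CAES, including the description on procedure, type of needle, and endoscopic images".

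**Primary outcome.** Under Outcome measures, a patient is counted as recurrent by any one of three routes:

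- Criterion (1): an unchanged-or-worse answer "at 24th week as reported by the patient".
- Criterion (2): "seeking repeat CAES treatment, alternative non-surgical/surgical treatments for internal hemorrhoids within 24 weeks (except medication treatment".
- Criterion (3): "presence of any symptoms or events that strongly indicated recurrent hemorrhoids among patients not meeting (1) or (2".

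**Retreatment.** Safety assessment and management says that "repeat CAES or other treatment options should be adopted if symptoms are not improved significantly or even worse than before".

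**Week 24.** The Discussion says that colonoscopy need not be repeated in the first half year. Outcome measures reserves endoscopy during follow-up for uncontrollable pain or bleeding, or for repeat treatment.

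**Expectation.** In the Conclusion the investigators state that they assume better efficacy, fewer adverse events and higher satisfaction with the long needle.

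**The concern.** The operator must know whether the needle is 14 mm or 4 mm, and the visible operation is a sound reason for not blinding that person. Recording a symptom answer 24 weeks later is a different act by a possibly different person, and the reason given does not reach it.

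This matters because the primary outcome is binary and symptom-based, and one of its routes is an unlisted judgement about what strongly indicates recurrence. If that judgement is made by someone who knows the needle and shares the stated expectation, ambiguous cases may be called recurrent more readily in the short-needle arm. Table 1 gives such a person a reason to do so: it presumes that the long needle treats prolapse as well as bleeding, and the short needle bleeding only. Blinding the patient does not protect a judgement made by staff, and bias in classifying the primary outcome cannot be removed at analysis.

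**Working it through.** **1. Does the stated reason apply to each step?**

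| Step | Needs knowledge of the needle? | Covered by the visible operation? |
|---|---|---|
| Injection | Yes | Yes |
| Taking the week-24 answer | No | No |
| Classifying criterion (3) events | No | No |

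**2. How exposed is each criterion to someone who knows the needle?**

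- Criterion (1) is the patient's answer. Staff can affect it only by how they ask.
- Criterion (2) is worded as the patient seeking treatment. Staff can affect it indirectly, because retreatment depends on whether symptoms are judged to have improved enough, and no judge is named.
- Criterion (3) needs a judgement. No assessor, list of events or masking is stated. It applies only to patients who do not meet (1) or (2), so it can only add recurrences, including in patients who report being cured or improved.

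**3. The plan's own figure.** Inputs from Proposed sample size: 10% against 16%, 80% power, 5% significance (two-sided assumed).

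- Without continuity correction: n = [1.960·√(2·0.13·0.87) + 0.842·√(0.10·0.90 + 0.16·0.84)]² / 0.06² = 491.99, so 492.
- With continuity correction: n' = (491.99/4)·[1 + √(1 + 4/(491.99·0.06))]² = 524.8, so 525. This matches the stated 525.
- 525 × 1.10 = 577.5, so 578, as stated.

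Blinding the outcome assessment changes none of these.

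**4. Illustration of what is at stake.** Assumptions, not document figures: true recurrence p = 13% in both arms (midway between 10% and 16%); unmasked judgement adds d points in the short-needle arm only; two-sided 5% chi-square test without continuity correction.

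Chance of p < 0.05 = Φ[(d − 1.96·SE₀)/SE₁] + Φ[(−d − 1.96·SE₀)/SE₁], where SE₀ = √(2·p̄(1−p̄)/n), SE₁ = √([p(1−p) + (p+d)(1−p−d)]/n) and p̄ = p + d/2.

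Worked case, n = 578 and d = 0.03: SE₀ = 0.02071 and SE₁ = 0.02069. The first term is Φ(−0.512) = 0.304 and the second is below 0.001, so the total is 0.305.

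| Added points | Extra patients (525 / 578 per arm) | n = 525 per arm | n = 578 per arm |
|---|---|---|---|
| 0 | 0 / 0 | 5.0% | 5.0% |
| 1 | 5 / 6 | 7.6% | 7.9% |
| 2 | 11 / 12 | 15.4% | 16.5% |
| 3 | 16 / 17 | 28.1% | 30.5% |

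**5. How many patients separate significance from non-significance?** At 525 per arm, 68 against 91 recurrences gives z = 1.98, while 68 against 90 gives 1.90. The threshold gap is 23 patients, or 4.4 points. At 578 per arm, 75 against 99 gives z = 1.97, a gap of 24 patients, or 4.2 points.

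**The case against.** The strongest reply is that this argues from silence. The Discussion sentence is true of the operator and does not say that follow-up staff will be unmasked. The article sends details of outcomes and follow-up to Supplementary Tables that are not shown, and it mentions a blinding unit among the recipients of serious adverse event reports. A full protocol may name a masked assessor. This stands to the extent that nobody can say unmasked staff will judge recurrence. It does not rescue the rationale: the article gives one reason for its blinding level, that reason stops at the procedure, and the article itself leaves criterion (3) to open judgement. The blinding unit is given no role in outcome assessment.

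Three stronger readings are tempting and are not supported:

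- *Follow-up staff will see the allocation in the app.* The app shows the allocation to the physician choosing the needle and receives the endoscopy report. No section says that follow-up data are entered there, or that those who collect them see the allocation.
- *Staff decide two of the three routes.* Criterion (2) is worded as the patient seeking treatment, and the retreatment sentence in Safety assessment and management is passive and names no decision-maker. Its trigger largely overlaps the unchanged-or-worse answer of criterion (1), though it is wider. Only criterion (3) plainly needs another person's judgement.
- *The false-positive rate will be 8% to 30%.* Those figures depend wholly on an assumed shift placed in one arm. The documents give no basis for its size.

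**Conclusion.** The point holds in this form: the reason given for single blinding applies to the operator and not to recording or classifying recurrence at week 24. Criterion (3) is the direct exposure. Criterion (1) is exposed only through the asking. Criterion (2) is exposed only through the decision to retreat, and masked classification would not remove that exposure, because the retreatment has already happened.

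The size cannot be derived from the documents. If 1 to 3 points were added in the short-needle arm under no true difference, the chance of a significant result would be about 8% to 30% instead of 5%. No addition leaves it at 5%. The sample size is unaffected. The change should be made, because it is cheap and the bias could not be repaired afterwards.

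**What to change.** 1. State that patients and outcome ascertainment are blinded and that the operator is not.
2. Have the patient self-complete the week-24 question, or have existing staff who were not in the procedure room read it out verbatim.
3. Have criterion (3) events classified by existing site staff from records with the needle type hidden.
4. If follow-up data are entered in the app, hide the allocation and the endoscopy report from those entering them.

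The indirect exposure of criterion (2) remains and should be acknowledged in the limitations.

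Cost: protocol wording and, if item 4 applies, a change of access rights. No new staff, visits or patients are needed. The downside is that small centres must arrange that the operator does not take the week-24 answer.

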## Conclusion

In summary, we assume that long injection needle for CAES could lead to better efficacy and less AEs, and achieve higher patient satisfaction than that observed with short needle. This multi-center randomized controlled study is expected to provide the solid evidence to guide endoscopists to perform CAES for internal hemorrhoids and move CAES forward.

